## Abstract

**Background:**

Dental implant placement may require a bone graft for vertical and horizontal alveolar ridge augmentation. Due to its osteoconduction, osteoinductive, and osteogenesis, autogenous bone graft characteristics are considered the standard gold treatment. However, autografts can promote postoperative morbidity and implicate difficulties concerning the graft adaptation to the recipient's bone since it can eventually avoid gaps. To overcome these issues, this trial will compare the performance of Plenum^®^ Oss 3D_β_ fit, an alloplastic graft, and a 3D-printed patient-specific graft based on β-tricalcium phosphate to the autograft procedure.

**Methods:**

This is a split-mouth randomized clinical study designed to evaluate the performance of personalized (patient-specific) bioceramic bone grafts (Plenum^®^ Oss 3D_β_ fit) for bone augmentation of the atrophic anterior maxilla in comparison to the autogenous bone graft. We hypothesize that the gain and maintenance of the grafted area volume and the quality of the newly formed bone tissue after eight months postoperative with the synthetic patient-specific graft will be superior to the autogenous bone graft. To assess the quantity and the quality of bone neoformation, volumetric and histological analyses will be performed.

**Discussion:**

The fabrication of medical devices by additive manufacturing presents advantages over conventional manufacturing processes, mostly related to the precision of geometry and anatomy. Additionally, the osteoconductive proprieties of β-tricalcium phosphate enable this synthetic bone substitute as an alternative solution over autogenous graft for bone defect reconstruction. Thus, patient-specific bone grafts can potentially improve patient satisfaction, reducing the need for autogenous bone grafts, consequently avoiding implications related to this type of treatment, such as patient morbidity.

**Trial registration:**

This study is registered in REBEC (Registro Brasileiro de Ensaios Clínicos): RBR-76wmm3q; UTN: U1111-1272-7773. Registration date: 14 September 2021.

## Administrative information

Note: the numbers in curly brackets in this protocol refer to SPIRIT checklist item numbers. The order of the items has been modified to group similar items (see http://www.equator-network.org/reporting-guidelines/spirit-2013-statement-defining-standard-protocol-items-for-clinical-trials/)

## Introduction

### Background and rationale {6a}

The placement of dental implants in atrophic jaws is always a challenging condition. Before implant placement, bone grafts are frequently recommended for vertical and horizontal alveolar ridge augmentation. The autogenous bone graft stands out among other bone grafts due to its osteoconduction, osteoinductive, and osteogenesis properties. Although autogenous bone grafts are considered the gold standard for the reconstruction/replacement of bone grafts, the use of autografts is limited by several factors: mainly due to the significant postoperative morbidity of the patient and the insufficient amount of donor tissue [1, 2].

These disadvantages have led to new materials and promising methods for tissue repair, especially for bone tissue. In addition, homogenous and heterogenous bone grafts may promote immunogenicity, limiting these grafts’ use in specific surgical protocols [3]. Nevertheless, even with rigorous processes for deproteinization of these grafts, there is still a theoretical risk of disease transmission [1, 2, 4–6]. Alloplastic bone grafts, in turn, are synthetic biomaterials classified according to their origin. The alloplastic materials of ceramic sources mainly include calcium phosphate phases, which are essential mineral phases constituent of teeth and bones [4, 7]. Among ceramics, calcium phosphates are ceramics with Ca/P molar ratios ranging from 0.5 to 2.0 and can be found in various types, known as hydroxyapatite (HA) and β-tricalcium phosphate (β-TCP). HA and β-TCP are biocompatible materials used as excellent bone substitutes [5, 8] due to their osteoconductive properties and protein absorption capacity. However, bioceramics have different rates of in vitro solubility, which reflects in the in vivo degradation, i.e., the greater the Ca/P molar ratio lower the solubility of bioceramics; thereby HA phase has slower reabsorption, while the β-TCP has a faster reabsorption rate [4, 9].

Ceramic bone grafts can also be classified in their presentation, such as block or particulate grafts. When significant bone reconstruction in height and thickness are desired, and the bone defect does not have walls to favor bone regeneration, bone block grafts are indicated since they present satisfactory and predictable results for bone reconstruction/replacement [1, 2, 8, 10–12]. Indeed, the results obtained support the use of ceramic block grafts, proving to be an extremely beneficial technique, as it guarantees a safe, biocompatible bone substitute with unlimited availability. It also reduces the patient’s postoperative morbidity by not involving a second surgical site for bone graft removal. In addition, during the execution of the block graft technique, one of the most critical moments of the surgical procedure is the preparation of the graft for its adaptation to the recipient, which requires the experience from the surgeon to avoid gaps between the graft and host bone, reducing the chances of success [10–14]. This step can be facilitated by using ceramic bone grafts from 3D printing, a technology developed by tissue engineering that has contributed to the planning and execution of bone reconstructions [10, 13–15].

From initial cone-beam computed tomography (CBCT) scans and intraoral scanning, bone substitute scaffolds can be created and designed individually on the patient’s bone defect. In this way, the adaptation between them is guaranteed, and both patient and surgeon benefit by reducing the procedure's time and the patient’s morbidity [13–17]. Clinical studies using 3D ceramic scaffolds for bone regeneration have already been carried out and have shown satisfactory results [10, 13–15], which ensure their clinical applicability. However, the literature still lacks randomized clinical studies.

Plenum^®^ Oss 3D_β_ fit is a patient-specific medical device printed with custom dimensions. This medical device consists of a porous structure based on β-TCP (≥ 95% of β-TCP), planned by DICOM (Digital Imaging and Communications in Medicine) images from CBCT and manufactured by additive manufacturing technology (3D printing), producing personalized bone graft with complex geometrics. This bone substitute works like a bone graft, supporting the tridimensional bone reconstruction. Furthermore, the Plenum^®^ Oss 3D_β_ fit is slowly reabsorbed by the organism, favoring the substitution of the graft to the newly formed bone during the healing process or tissue regeneration.

Thus, this split-mouth randomized clinical study aims to evaluate the effect of bioceramic bone grafts in patient-specific blocks (Plenum^®^ Oss 3D_β_ fit) in bone augmentation of the atrophic anterior maxilla in comparison to the autogenous bone graft. The biocompatibility tests were performed following the normative instruction, ISO 10993-1 – *Biological Evaluation of medical devices*. The results showed that Plenum^®^ Oss 3D_β_ fit its safety with concerning its cytotoxicity and toxicity, endorsing the performance of this study in humans.

### Objectives {7}

The primary objective of this clinical investigation is to evaluate the increase/maintenance of bone graft volume after eight months postoperative when a synthetic patient-specific block graft is used compared to an intra-oral autogenous graft. The secondary objectives include the analysis and characterization of the new bone formation according to the graft used; Plenum^®^ Oss 3D_β_ fit, or autogenous; surgical particularities arising from the type of graft, such as the adaptation of the graft in the host bone; and operative time. In addition, implant stability and the adverse effects from both grafts and surgical procedures performed to install each kind of graft will also be analyzed.

### Trial design {8}

This protocol refers to a randomized superiority trial. This is a prospective, open, single-center, positive-controlled study, with two parallel groups, assigned as a split-mouth model, whereupon each side of the mouth will be allocated as an independent unit and each patient will receive both treatments, test and control.

## Methods: participants, interventions, and outcomes

### Study setting {9}

The study will be performed with adult patients from the Implant Dentistry course at the School of Dentistry, São Paulo State University (Unesp), Araraquara, Brazil, looking for implant-supported oral rehabilitation and needing graft in the atrophic anterior maxilla (Fig. 1).

**Fig. 1 Fig1:**
[figure not shown]
Flowchart of the study

### Eligibility criteria {10}

To be enrolled in this study, patients must present bone insufficiency in the anterior region of the maxilla, with a minimum height of 7 mm and a width of less than or equal to 5 mm (assessed by CBCT), be over 18 (there are no age limit) years old, and have voluntarily signed the consent form. The exclusion criteria are patients who have general contraindications to the surgical procedure. These include patients who: are undergoing radiation in the head and neck region; have immunosuppression or immunodepression; are being treated or undergoing treatment with anti-resorptive drugs or drugs that alter bone metabolism (such as heparin, warfarin, cyclosporine, glucocorticoids, medroxyprogesterone acetate, cancer drugs, and thyroid hormone, prednisone, prednisolone, methylprednisolone, dexamethasone, cortisone, and triamcinolone); have an untreated periodontal disease; have poor oral hygiene; have uncontrolled diabetes; have psychiatric issues or unrealistic expectations; are pregnant (for women of childbearing potential is required contraception methods awareness); are lactating; and are smokers.

### Who will take informed consent? {26a}

The consent process will be done jointly by the principal investigator, or a member of his team already assigned to this task and the patient. The application of the term will be in the clinic, and in this consultation, participants will have the opportunity to ask questions, check visits, follow-up time, risks, and benefits of the study. In addition, the participants can take the term with them, to discuss with people they trust, if they wish. If the patient decides to participate in the study, the term must be rubricated by the responsible for the application and the patient, and be signed on the last page, always in two copies, one for the patient and another copy for being kept at the center until the end of the study. Upon completion of the study, the consent form will be stored by the sponsor.

### Additional consent provisions for collection and use of participant data and biological specimens {26b}

Not applicable; no ancillary studies are foreseen.

## Interventions

### Explanation for the choice of comparators {6b}

To allow the installation of dental implants in atrophic alveolar ridges, bone grafts must be previously performed for bone volume and height reconstruction. The autogenous graft stands out for its osteoconduction, osteoinductive, and osteogenesis properties, being considered the gold standard for this type of intervention [18].

### Intervention description {11a}

#### Tomography

All participants must undergo CBCT tests before the surgical procedure (T1), in post-surgical follow-up at 1 week (T2) and 8 months (T3).

#### Planning and production: patient-specific Plenum^®^ Oss 3D_β_ fit

A trained professional will perform the patient-specific block planning (Mimics and 3-Matic, Materialise, Belgium) from the DICOM files, manufactured by additive manufacturing in a 3D ceramic printer (CeraFab 7500 LITHOZ). The patient-specific (personalized) graft will be produced using Lithography-based Ceramic Manufacturing technology. The process involves printing the virtual model (previously designed and exported in an STL file) with β-TCP slurry. After finishing the printing process, the grafts will be cleaned with a solvent to remove excess resin inside the pores. Then, it will be sintered in a muffle furnace at 1000°C and sent for sterilization by gamma irradiation.

#### Preparation and installation of the autogenous bone graft and Plenum^®^ Oss 3D_β_ fit

The intra- and extra-oral asepsis will be performed with 0.12% and 2% chlorhexidine digluconate. Next, the local anesthesia will be applied with Articaine 4% 1:100.000 (Nova DFL, Brazil), followed by a linear incision over the alveolar crest and two vertical incisions. Next, the mucoperiosteal flap will be detached, and the autogenous bone graft collection will be started. A linear incision will also be made in the donor site, followed by a mucoperiosteal flap detachment and a mandible branch exposure. Trunk-conical drills and discs mounted in a straight handpiece will be used for osteotomy. After the graft removal, it will incubate in saline solution while the receptor site is prepared. Grooves will be performed in the receptor site to stimulate the vascularization, and the autogenous bone graft will be fixed in the anterior region of the maxilla by fixing screws. On the opposite side of the maxilla (test group), grooves will also be performed, and the 3D printed block will also be fixed by fixing screws. Then, a resorbable polydioxanone membrane, Plenum^®^ Guide (Plenum, Jundiaí, São Paulo, Brazil) will be used over 3 to 4 mm of the bone grafts, and the suture will be performed with Nylon 5.0 (Ethicon^®^, Jonhson & Jonhson, New Brunswick, Nova Jersey, EUA). All surgical procedures will be performed by the same professional.

#### Dental implants installation and biopsy

Eight months after the graft surgery, the patients will undergo implant placement surgery. The same aseptic care as described above will be performed. Following the local anesthesia, a linear incision will be made, a mucoperiosteal flap will be detached, and the fixing screws will be removed. Biopsies of the grafted areas will be obtained in the vestibular palatine sense direction [19] to involve the residual and new-formed bone without interfering with implant placement. The obtained biopsies will be immediately fixed in paraformaldehyde 4%. Then, the osteotomy sequence and implant placement will be performed, and the implants (Plenum, Jundiaí, São Paulo, Brazil) will be placed. The resonance frequency analysis (RFA) will measure the primary implant stability using Osstell^®^ (Integration Diagnostics AB, Goteborg, Switzerland). The measures will be performed on the mesial, distal, vestibular, and palatal regions. In the same surgical procedure, in the cases with high quantitative bone, mini-implants will also be used on the vestibule-palatine side for future histological analyses [19]. Finally, the suture will be performed using Nylon thread, Nylon Blue 5.0 (Techsuture^®^, Bauru, São Paulo, Brazil).

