#### Secondary endpoints

The secondary endpoints are as follows:Assess bone neoformation in the anterior region of the maxilla when the personalized block graft is used compared to the use of autogenous bone block graft. This will be done by evaluating the percentage of new-formed bone tissue, soft tissue, and the rate of residual material from the bone graftInvestigate whether the choice of bone graft interferes with the primary and secondary stability of implants installed in the region. Measures will be performed with RFA immediately after de implant placement and after 6 monthsEvaluate the influence of the graft on the maturation of newly formed bone tissue through the quantification of osteocalcin (OCN) from the biopsies retrieved just before the implant placementAssess the influence of the use of the graft type on the activity of osteoblastic cell differentiation through the quantification of morphogenetic protein-2 (BMP-2) from biopsies samplesEvaluate the influence of autogenous and personalized graft on collagen matrix production through alkaline phosphatase quantificationInvestigate the influence of the graft in the differentiation of endothelial cells through the quantification of vascular endothelial growth factor (VEGF)Evaluate the volume of mineralized new-formed bone tissue through micro-tomographic examinationsVerify the adaptation of the bone graft to the host boneEvaluate whether there is a difference in the operative time for performing the ceramic bone graft compared to the autogenous graft

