#### Implant stability analysis

The primary and secondary implant stability will be analyzed using the Osstell^®^ device (Osstell AB, Gothenburg, Sweden). This device determines the implant stability by the resonance frequency analysis. The system includes using a SmartPeg fixed to the implant through an integrated screw. The SmartPeg is excited by a magnetic impulse from the measuring probe of the portable instrument, and the implant stability coefficient (ISQ) is calculated from the response signal. Results are displayed on the instrument ranging from 1 to 100. The higher the ISQ number, the greater the stability of the implant.

Stability measurements will be obtained in two directions: buccal-palatal and mesiodistal. Values will be compared within groups about primary and secondary stability. They will also be compared between groups to assess whether there is a difference between implant stability in the test and control groups.

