## Statistical methods

### Statistical methods for primary and secondary outcomes {20a}

Data from this study will be analyzed for their distribution by the Shapiro-Wilk normality test. If the data are distributed according to normality, parametric tests will be used for the inferential analysis of the data. The comparison between groups in each experimental period will be performed using the unpaired *t*-test. The longitudinal evaluation of these data within each group will be evaluated using the ANOVA test for repeated samples complemented by the Tukey test. If the data are not distributed according to normality and the qualitative parameters, they will be analyzed inferentially using non-parametric statistical tests. The comparison between groups in each experimental period will be performed using the Mann-Whitney test. The longitudinal evaluation of these data within each group will be evaluated using the Friedman test complemented by the Dunn test. The BioStat software version 5.3 will be used to perform the statistical analysis of this project.

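### Implant stability yields several ISQ readings per side, no single value per side is named, and the planned unpaired test does not fit the split-mouth unit, so its error rate is off 5% in either direction

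*Protocol article*

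**What the plan says.** All places are in the protocol article.

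- **Dental implants installation and biopsy**, on primary stability: "The measures will be performed on the mesial, distal, vestibular, and palatal regions". On the implants themselves it says only that "the implants (Plenum, Jundiaí, São Paulo, Brazil) will be placed"; no number per side is given.
- **Implant stability analysis**, on the same device and endpoint: "Stability measurements will be obtained in two directions: buccal-palatal and mesiodistal". It continues: "Values will be compared within groups about primary and secondary stability", and then: "They will also be compared between groups to assess whether there is a difference between implant stability in the test and control groups". No mean, minimum or other single value per implant or per side is named.
- **Secondary endpoints** lists the "primary and secondary stability of implants installed in the region" as one of nine secondary endpoints, measured at placement and six months later.
- **Trial design {8}**: "each side of the mouth will be allocated as an independent unit and each patient will receive both treatments, test and control". **Sequence generation {16a}** randomises the two treatments to the right and left side of each patient.
- **Statistical methods {20a}**: "The comparison between groups in each experimental period will be performed using the unpaired" t-test, with Mann-Whitney when normality fails.

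**The concern.** Both named between-group tests assume that every observation is independent of every other. In this design two kinds of dependence are present.

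1. Readings on one implant, and implants in one graft, are repeats of one allocated side. Entered singly, they make the standard error too small.
2. The two sides of one patient share that patient's bone, healing and surgical session. An unpaired test leaves this shared variation in the standard error, which makes it too large.

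The first pushes the false-positive rate up and the second pushes it down. The plan does not fix the number of readings or say how they are combined, so the calibration of the ISQ p-value depends on unstated recording and data-handling choices. If those choices were made after ISQ data exist, they could follow the results. At stake is either a chance ISQ difference reported as a graft effect, or a real one missed by a test that almost never rejects.

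**Working it through.** **The plan's own figure.** The protocol gives no calculation for ISQ. Its 20 participants are sized on volume reduction (difference 11.90, SD 12.09, power 0.8, alpha 0.05). A two-sided two-sample t-test gives 17.2, so 18 per group; a paired t-test with zero correlation gives 18.2, so 19. Both are within 2 of 20. Nothing below changes that number.

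**Inputs from the protocol.** 20 patients, one side per graft in each; two or four readings per implant; unpaired t-test.

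**Assumed inputs.** The protocol gives no ISQ variance components. Total variance is set to 1 and split into patient (vp), side (vs), implant (vi) and reading (ve). Implants per side, K, is 1 or 2; readings per implant, R, is 2 or 4. A two-sided 5% level and no true difference are assumed.

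**Formulas.** Let m = vs + vi/K + ve/(KR), the variance of a side mean around its patient's level. The difference between graft means has true variance 2m/20, because the patient part cancels.

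- Readings entered singly: the unpaired test uses about 2/(20KR). Ratio of true to assumed variance: r = KR × m.
- Side means entered: the unpaired test uses 2(vp + m)/20. Ratio: r = m/(vp + m).
- Approximate false-positive rate: 2[1 − Φ(1.96/√r)].

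**Shares 30/30/20/20**

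| K × R | m | r, single readings | approx. error | r, side means | approx. error |
|---|---|---|---|---|---|
| 1 × 2 | 0.30+0.20+0.10 = 0.600 | 2 × 0.600 = 1.2 | 7.4% | 0.600/0.900 = 0.67 | 1.6% |
| 1 × 4 | 0.30+0.20+0.05 = 0.550 | 4 × 0.550 = 2.2 | 18.6% | 0.550/0.850 = 0.65 | 1.5% |
| 2 × 4 | 0.30+0.10+0.025 = 0.425 | 8 × 0.425 = 3.4 | 28.8% | 0.425/0.725 = 0.59 | 1.0% |

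**Shares 70/5/5/20**

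| K × R | m | r, single readings | approx. error | r, side means | approx. error |
|---|---|---|---|---|---|
| 1 × 2 | 0.05+0.05+0.10 = 0.200 | 0.4 | 0.2% | 0.200/0.900 = 0.22 | below 0.1% |
| 1 × 4 | 0.05+0.05+0.05 = 0.150 | 0.6 | 1.1% | 0.150/0.850 = 0.18 | below 0.1% |
| 2 × 4 | 0.05+0.025+0.025 = 0.100 | 0.8 | 2.8% | 0.100/0.800 = 0.13 | below 0.1% |

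**Simulation check** (20,000 runs per setting, t-tests), in the order 1 × 2, 1 × 4, 2 × 4:

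| Shares | Unpaired, single readings | Unpaired, side means | Paired, side means |
|---|---|---|---|
| 30/30/20/20 | 7.9%, 20.1%, 29.5% | 1.7%, 1.7%, 1.2% | 5.1%, 5.3%, 4.9% |
| 50/20/10/20 | 3.5%, 11.0%, 19.6% | 0.6%, 0.4%, 0.2% | 5.2%, 5.1%, 4.9% |
| 70/5/5/20 | 0.4%, 1.6%, 3.8% | 0.0%, 0.0%, 0.0% | 4.9%, 4.9%, 5.1% |

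Simulated rates for single readings run slightly above the approximation, because the pooled sample variance of clustered readings falls a little below 1. In this check only the paired test on one mean per side stays at 5% in every row. The unpaired test on side means is also calibrated if the two sides of a patient are uncorrelated (vp = 0).

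**The case against.** **The two reading schemes may not conflict.** Vestibular and palatal are the two ends of one axis, mesial and distal of the other, so four sites on two axes could satisfy both sections. That stands. It is too strong to say that one section takes four readings and the other takes two. What remains is that the text never makes the link, so the number of values per implant is open.

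**No statement says that readings are analysed singly.** This also stands. A reader might infer that repeat readings and extra implants count as extra patients and therefore inflate false positives. The protocol does not support that as fact. It names no unit for the ISQ comparison, and an averaging rule may sit in a fuller document not shown. Even on that reading, the error can fall below 5%, because ignoring the pairing works the other way.

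**Several implants per side is inferred from a plural.** Correct: the plural is natural with several patients and two sides each. A reader might go further and suppose that sides with better grafts receive more implants and more weight; nothing in the protocol supports that.

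**A missing averaging rule alone would be ordinary missing detail.** Agreed. The point survives because the unpaired test is stated and does not fit the allocated unit under either way of filling the gap, apart from the special case of uncorrelated sides or a chance offset of the two effects.

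**Conclusion.** The concern holds in a conditional form. The ISQ comparison as stated is generally miscalibrated, but the direction cannot be read from the protocol. Against a nominal 5%, the unpaired t-test gives about 8% to 30% on single readings with shares 30/30/20/20 and 0.4% to 4% with shares 70/5/5/20. On side means it gives about 0% to 2% across the three sets of shares. These figures rest on assumed variance shares, on one or two implants per side, and on positive correlation between the two sides of a patient. They illustrate the range and are not estimates for this trial. Implant stability is a secondary endpoint; the 20 participants and the volume comparison are not affected by this point.

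**What to change.** 1. Align the two sections on one reading scheme, used at placement and at six months. If the four regions are the ends of the two directions, say so and state how many values are recorded per implant.
2. In the stability section, define the analysed value: for each side and visit, average the readings on each implant, then average over any implants on that side. This gives one ISQ per side per patient per visit.
3. For the between-graft comparison, replace the unpaired tests by a paired test on the 20 within-patient differences: paired t-test, or Wilcoxon signed-rank if the differences are not normal.

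The cost is a few sentences and one averaging step. No new measurement, patient or change to care is needed. The change should be made before ISQ data are available.

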#### Healing caps placement

After 6 months of implant placement, healing caps will be placed to begin the prosthetic phase. The cover screw will be removed, RFA will check the secondary implant stability, and the healing cap installed. In the cases where mini-implants were used, they will be retrieved by trephine drills for posterior analysis [19].

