### Outcomes {12}

#### Primary endpoints

Evaluate the gain of increase/maintenance of the volume of the bone graft area and the quality of the newly formed bone tissue after eight months of the postoperative between the synthetic graft in a personalized block with the autogenous bone graft.

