##### Histomorphometric analysis

The paraffin blocks will be cut in serial cuts with 4μm thick along their entire length. To obtain the histological blades, the pattern of selecting the center cut of the block will be followed. Blades will be stained with hematoxylin and eosin (HE, Merck & Co. Inc., New Jersey, USA). Blades images will be captured and scanned using an optical microscope with fourfold magnification objectives and 5-fold magnification eyepieces (Diastar - Leica Reichert & Jung products, Germany), with a digital camera (DFC-300-FX, Leica Microsystems, Germany) with 1.3-megapixel resolution coupled to this microscope and connected to a microcomputer with a digitalized image analyzer software Image J 1,45 (Wayne Rasband National Institutes of Health, USA). The following parameters will be evaluated: newly formed bone percentage, soft tissue percentage, and residual bone graft percentage. Measurements will be performed by a single calibrated examiner blinded to experimental groups.

The mini-implant blocks with bone tissue will be cut at a central point using a cut and wear system (Exakt Apparatebeau, Hamburgo, Germany). The sections will be approximately 45 μm thick, stained with Stevenel’s blue associated with acid fuchsin, and analyzed under an optical microscope (DIASTAR – Leica Reichert & Jung products, Wetzlar, Germany) at × 100 magnification. Histomorphometric evaluations will be performed with the image analysis software (Image J, San Rafael, CA, USA). In addition, the percentages of bone-implant contact (%BIC) and the bone area between turns (%BBT) will be evaluated separately in the region between bone tissue and the center of the mini-implant. A blind and trained examiner will perform these analyses.

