### Sample size {14}

Sample calculations were performed based on tomographic bone formation data from the study, which evaluated the volumetric stability of autogenous and allogeneic corticomedullary block grafts used for volume increase associated with edentulous alveolar ridges [19]. This choice was due to the lack of studies comparing β-tricalcium phosphate blocks and autogenous bone and the similarity of the methodology for evaluating the stability of block grafts. As a result, it was verified that the minimum difference between the means of treatments concerning the percentage of volumetric reduction of the graft was 11.90, with a standard deviation of 12.09. Therefore, considering a study power (1-β) of 0.8 and an *α* power of 0.05, a minimum sample of 20 participants was determined, each of whom will receive two grafts, one synthetic in a personalized block and another in an autogenous block. To maintain the power of the study, the sample size should be maintained, thus if any participant dropout or is discontinued before the analysis of the primary outcome, a new participant will be recruited instead, until complete 20 participants.

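### %BIC and %BBT come only from mini-implants placed where bone is plentiful eight months after grafting, so any between-graft comparison of them is open to selection bias

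*Protocol article*

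**What the plan says.** All references are to the protocol article.

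- **When the sites are chosen** (Dental implants installation and biopsy): "Eight months after the graft surgery, the patients will undergo implant placement surgery". Randomisation and grafting are by then eight months in the past.
- **How they are chosen** (same section): "in the cases with high quantitative bone, mini-implants will also be used on the vestibule-palatine side for future histological analyses". No bone threshold is given, and a case is not defined as a patient or as one side of the maxilla.
- **Which sites give data** (Healing caps placement): "In the cases where mini-implants were used, they will be retrieved by trephine drills for posterior analysis".
- **What is measured** (Histomorphometric analysis): "the percentages of bone-implant contact (%BIC) and the bone area between turns (%BBT) will be evaluated separately". The sentence goes on to name a region of the mini-implant, so the separation is by region and not by graft. The examiner is blinded.
- **Status of the measures**: neither %BIC nor %BBT appears under Primary endpoints or Secondary endpoints.
- **The primary endpoint**: "increase/maintenance of the volume of the bone graft area and the quality of the newly formed bone tissue after eight months". The abstract's hypothesis is that these results "with the synthetic patient-specific graft will be superior to the autogenous bone graft".
- **The analysis** (Statistical methods {20a}): "The comparison between groups in each experimental period will be performed using the unpaired" t-test, or by Mann-Whitney if the data are not normal. The paragraph covers the study's data in general. Methods for additional analyses {20b} adds that every analysis is already described.
- **Blinding**: section {17a} calls the trial open, and one professional performs all surgery.

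**The concern.** Split-mouth randomisation makes the two sides comparable at the time of grafting. It protects a later comparison only if the sides that are measured are not picked by something the graft has changed. Here they are picked by the amount of bone at eight months, which is close to what the graft is meant to change.

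If one graft yields more bone, more of its sides pass the criterion, including ordinary ones. The other graft contributes only its best sides. Where bone quantity and %BIC go together, the second graft's %BIC is then flattered. The blinded histology examiner cannot correct this, because the selection was made at surgery, with the grafts known.

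At stake is a statement about osseointegration of one graft against the other that would look randomised and would not be.

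**Working it through.** **The plan's own figure.** The article gives no figure for %BIC, %BBT or the share of cases with mini-implants. Its only planning figure is in Sample size {14}: the difference in "percentage of volumetric reduction of the graft was 11.90, with a standard deviation of 12.09". The standardised effect is 11.90/12.09 = 0.984. An unpaired two-sided t-test at alpha 0.05 (two-sided is assumed; the article does not say) and power 0.80 needs 17.2, so 18 per group. With 20 per group the power is 0.858. The stated 20 is thus reproduced to within 2. It is used below only as one plausible size for a graft effect on bone quantity.

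**Assumptions (none is in the documents).**
- Bone quantity and %BIC are normal with SD 1 within each graft.
- Their correlation r is 0, 0.3 or 0.6.
- A side is selected when its quantity exceeds a cut-off c, set at 0 or 0.5 SD above the mean of the graft yielding less bone.
- The other graft shifts quantity by d = 0, 0.5 or 0.984 SD.
- The true %BIC difference is zero.

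**Formula.** Selected sides lie above their own graft's mean quantity by λ(x) = φ(x)/[1 − Φ(x)], with x = c − d for the graft yielding more bone and x = c for the other. The false %BIC difference is

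r × [λ(c − d) − λ(c)].

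The values needed are λ(0) = 0.798, λ(0.5) = 1.141, λ(−0.5) = 0.509, λ(−0.984) = 0.294 and λ(−0.484) = 0.517.

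| d | c | Selected: more-bone graft / other | λ(c − d) − λ(c) | r = 0.3 | r = 0.6 |
|---|---|---|---|---|---|
| 0 | 0 or 0.5 | equal | 0 | 0 | 0 |
| 0.5 | 0 | 69% / 50% | −0.289 | −0.09 | −0.17 |
| 0.5 | 0.5 | 50% / 31% | −0.343 | −0.10 | −0.21 |
| 0.984 | 0 | 84% / 50% | −0.504 | −0.15 | −0.30 |
| 0.984 | 0.5 | 69% / 31% | −0.624 | −0.19 | −0.37 |

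With r = 0 every entry is zero. A simulation with one million patients per setting agrees to within about 0.004 SD; its largest value was −0.378.

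**Keeping only patients selected on both sides.** With an assumed within-patient correlation of 0.5 in bone quantity and d = 0.984, the false difference shrinks to between −0.09 and −0.24 SD. It does not vanish. The share of patients with both sides selected is 47% (c = 0) or 27% (c = 0.5): 20 × 0.468 ≈ 9 or 20 × 0.271 ≈ 5 patients. The replacement rule in {20c} secures 20 biopsies, not 20 pairs of mini-implants.

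**If %BIC follows the graft's own shift in quantity.** The true difference is then r × d, and selection subtracts the same amount from it. At d = 0.984, r = 0.6 and c = 0.5, the true difference is 0.59 and the selected one 0.59 − 0.37 = 0.22 SD. The advantage shrinks but keeps its sign.

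**The case against.** The strongest reply is that nobody has promised this comparison. %BIC and %BBT are outside both endpoint lists, no hypothesis names them, and the histomorphometry section does not say that they will be compared between grafts. This stands in part: the comparison is inferred from the general wording of {20a}. But that wording makes no exception, and {20b} says that nothing further is planned, so the test applies as written.

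Four more points are fair.

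- The documents show neither a graft effect on bone quantity nor a link between quantity and %BIC. A reader might infer that the comparison is biased as a matter of fact; the text supports only that it is open to bias.
- If a case is a patient and both sides then receive mini-implants, pairing is kept and the side-level figures do not apply. A reader might infer that pairs are necessarily lost; the article does not settle this. The unpaired test in {20a} is a separate matter.
- A reader might infer that the better graft would come out worse. As shown above, that depends on whether %BIC rises with the graft's own gain in bone. If it does, the result is attenuation.
- Restricting mini-implants to sites with ample bone may be a matter of feasibility. That can justify where they are placed, but it does not make the selected sides comparable.

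It can also be said that subset definitions and exploratory labels belong in an analysis plan that is not shown. The selection rule itself, however, is stated in the article, and no later analysis restores the randomisation for this subset.

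**Conclusion.** The point holds in a limited form. The %BIC and %BBT data come from a subset chosen after randomisation, by an undefined criterion close to the primary outcome, and the plan's generic between-group test would be applied to them. Such a comparison does not have the protection of the split-mouth randomisation.

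The direction, if bias arises, is against the graft that yields more bone. Its size cannot be determined from the documents. It ranges from zero, when either condition fails, to about 0.37 SD at the largest inputs tried. Those inputs are assumptions. The 0.98 SD effect in particular is borrowed from the planning figure for volumetric reduction, which came from a study of allogeneic and autogenous blocks.

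A reader might take this as a threat to the trial's main findings. It is not: no listed primary or secondary endpoint is measured on the mini-implants.

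**What to change.** In Histomorphometric analysis and in Statistical methods {20a}:

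1. State that %BIC and %BBT are exploratory and descriptive, and exclude them from the between-group tests.
2. State whether a case is a patient or a side.
3. Commit to reporting, by graft, how many sides received a mini-implant.
4. Optionally add a display limited to patients with mini-implants on both sides, with a note that this reduces the selection bias but does not remove it.

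The surgical decision on where mini-implants are placed stays as it is; no numeric placement threshold is proposed.

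The cost is wording only, and the article reports that recruitment had not yet begun. The downside is that %BIC and %BBT can no longer support a claim that one graft does better than the other.
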